### 2.8. Patient Treatment and Follow-Up

Treatment with niclosamide (single oral dose, 2 g) or praziquantel (10 mg/kg) (depending on the availability of the drugs) was offered to patients who tested positive for T using the TS POC T or any of the reference tests. Relatives of these patients were also informed and invited for a diagnostic test, and in the case of positivity, treatment was offered. 

Patients who underwent a CT scan were informed about the results during a follow-up appointment, and management procedures as described for the community-based study in Zambia were followed [11]. In short, if indicated, anthelmintic treatment was offered according to national guidelines and Winkler et al. If indicated, anthelmintic treatment with albendazole (15 mg/kg/d) was offered for 10 days, accompanied with corticosteroid treatment (dexamethasone 12 mg to 20 mg/d), starting one day before and ending three days after anthelmintic treatment with half the dosage. Dexamethasone dosage depended on the location and number of cysticerci [21]. Symptomatic NCC cases with active lesions were treated with anthelminthic medication and steroids for two weeks according to the patient’s response. Treatment was tailored to each individual patient. At set time points (after six weeks and again after six months), a follow-up clinical examination was performed. During these time points, follow-up CT scans were offered to monitor treatment success. 

### 2.9. Training

Training and capacity building were cornerstones of the project. Extensive multiple full-day training sessions were organized at the district hospitals to ensure the collection of high-quality data and correct patient management and follow-up. Three-day training sessions were arranged where everyone involved in the project was trained. Sessions on parasite biology, diagnosis, treatment, prevention, and control of the parasite in endemic areas were organized for all project staff members. 

Tailored training was organized for clinicians responsible for recruiting patients, nurses responsible for obtaining informed consent and TS POC testing, and laboratory technicians responsible for blood and stool sample collection and processing. Medical doctors responsible for clinical examinations, including the neurological examination and later patient follow-ups and treatment were trained by the neurology team, contributing to capacity building in the study area. Assessments and follow-up refresher training were planned to assure the correct following of study procedures and good clinical (laboratory) practices and sample collection. Monitoring visits to assess study conduct and compliance on good storage of TS POC tests, samples, and other study material were conducted twice a month. If deviations from standard operating procedures were encountered, corrective measures were initiated.

### 2.10. Data Management

To ensure the collection of high-quality data, all people involved in patient recruitment and performing the POC test were trained and followed up regularly by project members. Non-confidential data were collected electronically on tablets using EpiCollect5 (© 2021 Centre for Genomic Pathogen Surveillance, v4.2.0, https://five.epicollect.net, accessed on 8 July 2021). Specific CRFs were created, and real-time data validation rules were included whenever possible. More details can be found in [11].

Laboratory technicians performing the reference tests were blinded to the TS POC results. Reading of the CT scans was carried out by two independent readers, both blinded to the TS POC and reference tests results. Discrepancies between two readers were identified and solved by a third reader, who was also blinded to the TS POC results.

### 2.11. Sample Size and Statistical Analysis

The sample size for group 1 was calculated to obtain the desired half-width of 5% around the 95% confidence interval for sensitivity and specificity [22]. Assuming a sensitivity of 93%, a specificity of 99% [11], and a prevalence of NCC of 20%, 500 participants were required. To account for losses, 20% were added to this number. The final sample size for group 1 was set at 600.

Since the prevalence of T in the study population was unknown, the sample size for groups 2 and 3 was calculated for different plausible values, ranging between 3% and 10%. Assuming a sensitivity of 82%, a specificity of 81%, and the desired precision of 10%, 1890 participants were required. To account for 5% contingencies, the final sample size was rounded to 2000 patients.

The sensitivity and specificity of the TS POC test for the detection of T, CC, and NCC were determined relative to the reference tests as shown in Table 1, for each of the three study groups. Weighting was used to correct for the study design (a subset of T-CC that is selected for sampling/clinical examination). The positive and negative predictive values were also determined.

For T and CC, the diagnostic sensitivity and specificity of the TS POC test were estimated using a Bayesian approach as described previously [23]. For the evaluation of the TS POC test performance for NCC, sensitivity and specificity were computed by cross-tabulating POC results with those of the final NCC diagnosis. More details can be found in [11].

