**Figure 3 diagnostics-11-01528-f003:**
[figure not shown]
Flow of the diagnostic accuracy study in Tanzania for patients attending the mental health ward or outpatient department of district hospitals with on-going symptoms of severe progressive chronic headache impeding their daily activities without fever and signs of cerebral infection or other obvious causes; and/or a history of one or more epileptic seizures without obvious causes (group 1). In this two-stage design, all patients were tested using the TS POC test (=index test; stage 1), after which all positive, and a subset of negative, patients were selected for different reference tests, clinical examination, and a brain CT scan (stage 2).

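### The 500 and 1890 patients assume that everyone is verified, but only a subset of index-negatives is, so the stated precision for sensitivity is too favourable at the sizing inputs

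*Protocol article*

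**What the plan says.** Section 2.11 states the aim for group 1: "The sample size for group 1 was calculated to obtain the desired half-width of 5% around the 95% confidence interval for sensitivity and specificity". With a sensitivity of 93%, a specificity of 99% and "a prevalence of NCC of 20%, 500 participants were required", it then allows for dropout: "To account for losses, 20% were added to this number. The final sample size for group 1 was set at 600".

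For groups 2 and 3 the taeniosis prevalence was unknown, so the size was "calculated for different plausible values, ranging between 3% and 10" per cent. The result is: "Assuming a sensitivity of 82%, a specificity of 81%, and the desired precision of 10%, 1890 participants were required". A 5% contingency brings this to 2000.

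The Figure 3 caption describes verification in group 1: "all positive, and a subset of negative, patients were selected for different reference tests, clinical examination, and a brain CT scan". The Abstract says the same, and the Figure 4 caption applies the same rule to the reference tests in groups 2 and 3. Section 2.11 adds that weighting corrects for the sampled subset. None of the text shown gives the sampled fraction.

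**The concern.** A case that the index test misses enters the data only if that index-negative patient happens to be sampled for stage 2. Each such case then stands for 1/f cases, where f is the verified fraction of index-negatives. Weighting makes the sensitivity estimate unbiased, but its variance is driven by the few false negatives that were actually seen. A sample size that treats all diseased patients as verified therefore understates the width of the interval.

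Sensitivity is part of the primary objective (Section 2.3) and is the quantity that fixed both sample sizes. The Discussion links a successful validation to commercialization and implementation, so readers will take the 5% and 10% as what the study can deliver.

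**Working it through.** **Inputs from Section 2.11.** Group 1: sensitivity (Se) 0.93, specificity (Sp) 0.99, prevalence 0.20, half-width 0.05, N = 500 (600 with losses). Groups 2 and 3 together: Se 0.82, Sp 0.81, prevalence 0.03 to 0.10, half-width 0.10, N = 1890 (2000 with contingency). Section 1 gives a local copro-antigen prevalence of taeniosis of 5.2%. The fraction f is not given and is varied here as an assumption.

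**Step 1: reproduce the plan.** N = 1.96² × Se(1 − Se) / (d² × prevalence).

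- Group 1: 1.96² × 0.93 × 0.07 / 0.05² = 100.0 cases; divided by 0.20 this is 500.2. Stated: 500.
- Groups 2 and 3: 1.96² × 0.82 × 0.18 / 0.10² = 56.7 cases; divided by 0.03 this is 1890.1. Stated: 1890.

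Specificity alone would need about 19 patients (1.96² × 0.99 × 0.01 / 0.05² / 0.80) and 61 patients (1.96² × 0.81 × 0.19 / 0.10² / 0.97). Sensitivity therefore drives both sizes, and the match leaves no room for a term for partial verification.

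**Step 2: two-stage variance (Begg-Greenes type).** All index-positives and a random fraction f of index-negatives are verified. Write p1 and p0 for the index-positive and index-negative shares. Then

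half-width = 1.96 × Se(1 − Se) × √[ 1/(N p1 p0) + (1 − PPV)/(PPV N p1) + NPV/((1 − NPV) f N p0) ].

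Group 1: p1 = 0.20 × 0.93 + 0.80 × 0.01 = 0.194, PPV = 0.186/0.194 = 0.959, 1 − NPV = 0.014/0.806 = 0.0174. At N = 500 the three terms are 0.0128, 0.0004 and 0.1404/f. At f = 1 this gives 1.96 × 0.0651 × √0.1536 = 0.050, the planned value. Nearly all the variance sits in the term divided by f.

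Groups 2 and 3 at 3%: p1 = 0.0246 + 0.97 × 0.19 = 0.2089, PPV = 0.118, 1 − NPV = 0.0054/0.7911 = 0.0068. At N = 1890 the terms are 0.0032, 0.0190 and 0.0973/f. At f = 1 the half-width is 0.100, again the planned value.

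**Step 3: half-width for sensitivity, in percentage points.**

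| Setting | f = 1 | 0.75 | 0.5 | 0.25 |
|---|---|---|---|---|
| Group 1, N = 500 | 5.0 | 5.7 | 6.9 | 9.7 |
| Group 1, N = 600, no losses | 4.6 | 5.2 | 6.3 | 8.8 |
| Groups 2 + 3, 3%, N = 1890 | 10.0 | 11.3 | 13.5 | 18.6 |
| Groups 2 + 3, 3%, N = 2000, no losses | 9.7 | 11.0 | 13.1 | 18.0 |

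A simulation with 40,000 replicates agrees. For N = 600 it gives 6.3 and 8.7 at f = 0.5 and 0.25; for N = 2000 at 3% it gives 13.0 and 17.7.

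**Step 4: smallest f that meets the target with the full N and no losses.** Group 1: 0.82. Groups 2 and 3: 0.93 at 3% prevalence, 0.49 at 5.2% and 0.24 at 10%. For example, with N = 2000 the half-width is 9.9 points at 5.2% and f = 0.5, and 9.8 points at 10% and f = 0.25.

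**Step 5: verified false negatives.** Group 1, N = 600: 600 × 0.20 × 0.07 = 8.4 expected, of which 4.2 are verified at f = 0.5 and 2.1 at f = 0.25. Groups 2 and 3, N = 2000 at 3%: 2000 × 0.03 × 0.18 = 10.8 expected, of which 5.4 and 2.7 are verified.

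**Step 6: specificity.** Its half-width stays near 0.9 points (group 1) and 1.75 points (groups 2 and 3), almost independent of f.

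**The case against.** The strongest reply is that the deciding input is not visible. The flow charts are not shown, and Section 2.11 refers to the companion Zambian design paper for detail. With a high f and no losses, the enlarged samples would cover the targets. This stands. It makes the size of the shortfall a range, but it does not rescue the calculation, because the added patients are labelled as losses and contingencies and not as cover for partial verification.

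Section 2.7 can be read as full examination in group 1: it says that a doctor saw all group 1 patients and then describes CT after the neurological examination. On that reading f is about 1 for NCC and the 5% holds. The Abstract and the Figure 3 caption say otherwise, and the text has to be reconciled.

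For groups 2 and 3, the 1890 is the most demanding case in the 3% to 10% range. Over much of that range the 10% target tolerates moderate subsampling, as Step 4 shows. This also stands, although the low end was evidently the case that the size was meant to protect.

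If a patient positive on either strip counts as positive, only double-negatives are subsampled, and the loss is somewhat smaller. Suppose 19% of patients were positive on the other strip, independently (an assumption). In group 1 with N = 600 and f = 0.25, the average of 1/f then falls from 4 to 0.19 + 0.81 × 4 = 3.43, and the half-width falls from 8.8 to 8.2 points. The effect is modest.

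Finally, no test, success threshold or stopping rule depends on the half-width, and recruitment has ended. This lowers the severity but does not make the stated precision correct.

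**Conclusion.** The point holds as a should-fix. As written, 500 and 1890 deliver half-widths of 5% and 10% for sensitivity only if every enrolled patient is verified, and the design described does not do that. After the planned losses, any f below 1 misses the stated precision at the sizing inputs. Without losses, the half-widths are 6.3 (group 1) and 13.1 points (groups 2 and 3 at 3%) at f = 0.5, and 8.8 and 18.0 points at f = 0.25. These figures assume random sampling of index-negatives, a reference standard taken as correct, the plan's own accuracy inputs, and groups 2 and 3 pooled.

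Three stronger conclusions might be inferred and are not supported:

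- That the precision is definitely lost everywhere. The text shown does not give f, and the 10% target survives for f of about 0.49 or more at 5.2% prevalence and 0.24 or more at 10%.
- That the intervals become extreme at very small f. At f = 0.10 only about one verified false negative is expected (0.84 and 1.08), and the large-sample formula is unreliable there.
- That the Bayesian analysis for taeniosis and cysticercosis would be wider still. This was not computed, and the method's details are in a cited source that is not shown.

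Specificity is not at issue.

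**What to change.** 1. State f, the fraction of index-negatives selected for verification, for group 1 and for groups 2 and 3.
2. Reconcile Section 2.7 with the Abstract and the Figure 3 caption on who was verified in group 1.
3. In Section 2.11, replace the 5% and 10% claims for sensitivity with the expected half-widths from the two-stage variance at that f. For groups 2 and 3, give them across 3% to 10% prevalence. The specificity precision can stay.
4. For the NCC cross-tabulation, report intervals that account for the verification weights.

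The cost is about a paragraph of text and a less favourable stated precision. No patients are added.

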### 2.2. Study Design, Recruitment, and Eligibility

To evaluate the diagnostic performance of the TS POC test for the detection of T, CC, and NCC, a prospective, two-stage, multicenter study was conducted. The TS POC test was evaluated at the stage where it may be implemented in practice, being patients attending district hospitals in *T. solium*-endemic areas. Since the accuracy of the test was likely to vary across subgroups of patients [15], the study was performed on three groups of patients, namely patients with specific neurological signs and symptoms (epilepsy and/or severe progressive chronic headache) (group 1); patients with complaints compatible with intestinal worm infections (group 2); patients with other symptom(s) (group 3). To get a representative sample for the studied populations, subjects for groups 1 and 2 were consecutively recruited, while for group 3, only every tenth patient was included if eligibility criteria were met. Recruitment took place between December 2017 and February 2020. 

Patients of group 1 were recruited from the mental health ward or the outpatient department while patients belonging to groups 2 and 3 were recruited from the outpatient department only. To be included, patients had to be ten years old or above and willing and able to participate in all aspects of the study (including providing blood and stool samples, undergoing a clinical examination, and a brain CT scan, if necessary), willing and able to provide written informed consent (assent for minors with consent from a parent or a legally authorized representative), living in the study area for the past three months and planning to stay in the same area throughout the study period. Pregnant women and patients suffering from severe health conditions needing in-patient care were excluded from the study. 

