## 3. Discussion

This trial was designed to provide a rigorous evaluation of TS POC test accuracy for the detection of T, CC, and NCC. The ambitious four-year project was the result of longstanding North–South collaborations and aimed at including 2600 patients of three district hospitals in Tanzania. If the test is validated with success, it may be proposed for commercialization and implementation at district hospitals and community health centers in endemic areas. 

As several sources of bias can arise in diagnostic accuracy studies [24], several measures were taken to assure the internal validity of our study. As unblinded studies may have a higher sensitivity and overall accuracy of results when the person interpreting the reference standard is aware of the index test result [25], diagnostic review bias in the present study was avoided by blinding all laboratory technicians to the TS POC test result. Moreover, as the interpretation of several reference test results for T and CC have inherent test integrity (such as ELISA results, which are read by a spectrophotometer), diagnostic review bias seemed very unlikely for the evaluation of T and CC. On the other hand, clinical examination, and interpretation of CT scans, which were both used for the composite case definition for NCC, are more subjective. Therefore, a structured questionnaire was used to record the results of the neurological examinations to reduce subjectivity in the examinations as much as possible. Moreover, all CT scans were read in detail by two independent readers, and in the case of a disagreement, additionally by a third independent reader, who were all blinded to the TS POC result. 

Stool and serum samples for the reference tests were requested immediately after performing the TS POC test to reduce loss-to-follow-up and to avoid disease progression bias. Although we aimed to perform the CT scans with minimal delay, the CT scans could not always be performed within a reasonable time frame after the index test due to several logistical reasons (such as an inoperative CT scanner and travel planning of the neurology team to be present when CT scans were taken). Since delayed verification may result in biased accuracy estimates [25], an additional TS POC test was performed on patients for whom more than two months had passed between the initial TS POC test and CT scanning. These results were used to assess the extent of disease progression bias.

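### The 2000 patients are sized for groups 2 and 3 combined, but accuracy is determined per group, so per-group taeniosis sensitivity falls short of ±10 points at the low end of the planned prevalence range

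*Protocol article*

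**What the plan says.** Section 2.11 gives one calculation for groups 2 and 3, driven by taeniosis: "the sample size for groups 2 and 3 was calculated for different plausible values, ranging between 3% and 10" per cent. The result is: "Assuming a sensitivity of 82%, a specificity of 81%, and the desired precision of 10%, 1890 participants were required". Then: "To account for 5% contingencies, the final sample size was rounded to 2000 patients". Group 1 is sized separately, for neurocysticercosis: "The final sample size for group 1 was set at 600".

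The Discussion gives the overall target; the study "aimed at including 2600 patients of three district hospitals in Tanzania".

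On the analysis, section 2.11 says that sensitivity and specificity for "T, CC, and NCC were determined relative to the reference tests as shown in Table 1, for each of the three study groups". Section 2.2 gives the reason for having separate groups: "Since the accuracy of the test was likely to vary across subgroups of patients".

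The captions of Figures 3 and 4 say that all index-test-positive patients, but only some of the negative ones, go on to the reference tests. Section 2.11 says that weighting corrects for this. The article gives neither the split of the 2000 between groups 2 and 3 nor the fraction of negatives verified.

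**The concern.** A precision target belongs to a particular estimate. Here the patient number is worked out as if groups 2 and 3 were one sample, while the estimates named in the next paragraph are per group. The article names no combined group 2 and 3 estimate, and its own rationale for the groups, that accuracy probably differs between them, argues against relying on one.

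A reader of section 2.11 will naturally attach the 10% to the per-group results described next. Taeniosis sensitivity is part of the primary objective (section 2.3), and the Discussion links successful validation to commercialization and implementation. Readers who judge a group's sensitivity should therefore know what precision the design can give it.

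**Working it through.** **Inputs.** From section 2.11: sensitivity (Se) 82%, specificity (Sp) 81%, precision 10%, prevalence 3% to 10%. From the Introduction: 5.2%, an area estimate of taeniosis prevalence by copro-antigen ELISA. Two readings are assumed: that the 10% is a half-width and that the confidence level is 95%, as stated for group 1 ("desired half-width of 5% around the 95% confidence interval for sensitivity and specificity"). Both are supported by the match in step 1.

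**1. The plan's own figure.** N = z² × Se(1 − Se) / (d² × prevalence).

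- At 3%: 1.96² × 0.82 × 0.18 / (0.10² × 0.03) = 1890. This matches exactly and corresponds to 1890 × 0.03 = 56.7 expected cases.
- At 10% the formula gives 567, so the low end of the range set the size.
- For specificity it gives 61 to 66, so sensitivity drives the number.
- Contingency: 1890 × 1.05 = 1985, or 1890 / 0.95 = 1989; either rounds to 2000.
- Check on group 1 (Se 93%, d 5%, prevalence 20%): 500, again as stated.

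**2. Is 2000 combined or per group?** 600 + 2000 = 2600, the stated total. Two groups of 2000 would give 600 + 4000 = 4600, more than the 3000 tests that section 2.1 says were produced. So 2000 covers both groups.

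**3. Half-width for sensitivity, full verification.** Half-width = 1.96 × √(0.82 × 0.18 / (n × prevalence)), in percentage points. The per-group columns assume an equal split: 1000 enrolled, or 945 evaluable (1890 / 2).

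| Prevalence | Combined 1890 | Combined 2000 | Per group 1000 | Per group 945 |
|---|---|---|---|---|
| 3% | 10.0 | 9.7 | 13.7 | 14.1 |
| 4% | 8.7 | 8.4 | 11.9 | 12.2 |
| 5% | 7.7 | 7.5 | 10.6 | 11.0 |
| 5.2% | 7.6 | 7.4 | 10.4 | 10.7 |
| 6% | 7.1 | 6.9 | 9.7 | 10.0 |
| 10% | 5.5 | 5.3 | 7.5 | 7.7 |

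At 3% the per-group number of cases is 30 (n = 1000) or 28 (n = 945). The prevalence at which a group reaches ±10 points is 56.7 / 1000 = 5.7% or 56.7 / 945 = 6.0%. Wilson intervals change little: half-widths of 13.4 and 13.8 at 3%.

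**4. Does the split matter?** At 3%, one group alone needs 1890, so both need 2 × 1890 = 3780. No division of 2000 achieves that. For example, 667/1333 gives 16.8 and 11.9 points, and 500/1500 gives 19.4 and 11.2.

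**5. Specificity.** Per group of 1000 at 3%: 1.96 × √(0.81 × 0.19 / 970) = 2.5 points; at 10%, 2.6. The target is met with a wide margin.

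**6. Partial verification (illustration).** Let f be the fraction of test-negatives verified. The article does not give it; 0.25 and 0.5 are assumptions. For the weighted estimate, the delta method gives half-width ≈ 1.96 × Se(1 − Se) × √(1/TP + 1/(f × FN)), where TP and FN are the expected true positives and false negatives.

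- Combined, n = 1890, 3%, f = 0.25: TP = 46.5, f × FN = 2.55; 1.96 × 0.1476 × √(0.0215 + 0.392) = 18.6 points. With f = 0.5: 13.5 points.
- Per group, n = 945, 3%, f = 0.25: TP = 23.2, f × FN = 1.28; 1.96 × 0.1476 × √(0.043 + 0.784) = about 26 points.

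With one to three verified false negatives expected, a symmetric interval is only a rough guide. These figures show direction and order of magnitude.

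**The case against.** The strongest reply is that nothing is miscalculated. The 1890 is right, the combined target is met under its own assumptions (9.7 points with 2000 at 3%), and section 2.11 never expressly promises ±10 points in each group. That stands. A reader might infer an arithmetic error or a broken per-group promise, and the article supports neither. What remains is a precision figure placed directly before an analysis to which it does not apply, without saying so.

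The shortfall is also partial. It concerns sensitivity only, and with an equal split and full verification it disappears above about 6%, which is more than half of the planned range. The split is not stated, and one prevalence is applied to both groups although group 2 is selected for worm-type complaints and may have more cases. The 5.2% comes from an area survey, not from hospital patients. All of this limits the size of the point. It does not remove it, because 3% is the value the plan itself used to set the number, and at 3% in both groups no split works.

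One might also infer that the combined estimate has ±10 points across the whole 3% to 10% range. That cannot be taken from the article either: it holds only under full verification, and only a subset of test-negatives is verified. The Bayesian analysis without a gold standard adds uncertainty that the formula ignores.

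Finally, one might read the absence of planned precision for taeniosis in group 1, or for cysticercosis, as a further fault. Sizing on selected targets is ordinary practice, and a condensed article may leave such detail to the full protocol. That is not part of this point.

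**Conclusion.** The point holds as a mismatch between the unit used for sizing (groups 2 and 3 combined) and the unit used for reporting (each group). At the low end of the planned range, per-group taeniosis sensitivity does not have ±10-point precision. At 3% prevalence the half-width is about 13.7 to 14.1 points, roughly 1.4 times the stated 10.

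The exact sizes rest on an equal split, the same prevalence in both groups, full verification and a perfect reference. The failure of at least one group at 3% does not depend on the split. Incomplete verification would widen both the combined and the per-group intervals, by an amount that the article does not allow one to fix.

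No estimate is biased by this, and the reported intervals will show their true width. It should be corrected, but it does not undermine the study.

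**What to change.** In section 2.11:

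- State that the ±10 points refers to taeniosis sensitivity in groups 2 and 3 combined, at 3% prevalence or above, assuming full verification.
- Give the expected half-width per group, and for the two groups combined, over 3% to 10% prevalence. Compute these with the planned split and the actual fraction of test-negatives verified. The full-verification table above should not be printed as the expected precision, because it is a best case.
- State whether the combined or the per-group estimate is the main taeniosis result.

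The cost is a short recalculation and a few sentences. Recruitment ended in February 2020 (section 2.2), so the sample cannot change, and the correction needs no further patients.

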## Abstract

*Taenia solium* diagnosis is challenging as trained personnel, good diagnostic tools, and infrastructure is lacking in resource-poor areas. This paper aims to describe the study trial design adopted to evaluate a newly developed rapid point-of-care test that simultaneously detects taeniosis and neurocysticercosis (TS POC) in three district hospitals in Tanzania. The two-stage design included three types of patients: patients with specific neurological signs and symptoms (group 1); patients with complaints compatible with intestinal worm infections (group 2); patients with other symptom(s) (group 3). For group 1, all patients were tested using the TS POC test (stage 1), after which all positive, and a subset of negative, patients were selected for laboratory reference tests, clinical examination, and a brain computed tomography (CT) scan (stage 2). For groups 2 and 3, a similar design was adopted, but clinical examination and a brain CT scan (stage 2) were only performed in patients who were TS POC test-positive for cysticercosis. Due to the lack of a gold standard, a Bayesian approach was used to determine test accuracy for taeniosis and cysticercosis. For neurocysticercosis, a composite case definition was used as the reference standard. If successful, this study will help the future developments (commercialization and implementation) of the rapid test and improve patient management and disease prevention.

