### 2.3. Study Objectives and Outcomes

The primary objective of the study was to assess the sensitivity and specificity of the TS POC test for the diagnosis of each of the disease presentations (T, CC, and NCC). Due to the lack of a gold standard, three different reference tests were used for the detection of T and CC, respectively (Table 1). The diagnostic accuracy of the TS POC test for the detection of T was determined against two stool-based reference methods (copro antigen ELISA and copro PCR) and a serological test (immunoblot using the recombinant protein rES33). For CC, the reference methods were the EITB-LLGP, rT24H immunoblot, and the B158/B60 monoclonal antibody-based serum antigen ELISA. For NCC, a composite case definition was used as the gold standard based on Del Brutto’s criteria [8]. An overview of the different reference tests included is given in Table 1, and a description of the tests is presented in Section 2.6.

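### At 3% prevalence, the 10% precision for taeniosis sensitivity is a best case, because 1890 comes from a known-status formula and the analysis has no gold standard

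*Protocol article*

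**What the plan says.** All statements are in the protocol article.

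- **Sample size (section 2.11).** Because the prevalence of taeniosis (T) was unknown, "the sample size for groups 2 and 3 was calculated for different plausible values, ranging between 3% and 10" per cent. The result is: "Assuming a sensitivity of 82%, a specificity of 81%, and the desired precision of 10%, 1890 participants were required". Then: "To account for 5% contingencies, the final sample size was rounded to 2000 patients".
- **Meaning of precision (section 2.11).** For group 1 the target is spelled out: "The sample size for group 1 was calculated to obtain the desired half-width of 5% around the 95% confidence interval for sensitivity and specificity". For groups 2 and 3 only a precision of 10% is named.
- **Reference standard (section 2.3).** "Due to the lack of a gold standard, three different reference tests were used for the detection of T and CC, respectively (Table 1"). For T these are the copro-antigen ELISA, the copro PCR and the rES33 immunoblot. The article gives no accuracy for any of them.
- **Analysis.** The Abstract says: "Due to the lack of a gold standard, a Bayesian approach was used to determine test accuracy for taeniosis and cysticercosis". Section 2.11 repeats it: "For T and CC, the diagnostic sensitivity and specificity of the TS POC test were estimated using a Bayesian approach as described previously".
- **Verification (Abstract, Figure 4 legend).** All patients positive on the point-of-care (POC) test go on to the reference tests, but only a subset of the negatives. Section 2.11 corrects for this by weighting. The fraction is not stated.

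**The concern.** The sample size and the analysis rest on different premises. The formula behind 1890 divides the binomial variance of sensitivity by a count of patients known to be infected. The analysis treats infection as unobserved and infers it from the strip and three imperfect references. Uncertainty about who is infected then adds to the variance of sensitivity, even if every patient has every test. Verifying only some test-negatives adds a further loss. The only stated addition to 1890 is the 5% contingency.

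Sensitivity for T is part of the primary objective. A reader who takes the 10% at face value would expect a tighter interval than the planned analysis can give if prevalence is near 3%, the value that set the size.

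**Working it through.** **1. Reproducing the plan's figure.** Inputs from section 2.11: sensitivity 0.82, specificity 0.81, precision d = 0.10, prevalence 3% to 10%. I read precision as the half-width of a two-sided 95% interval. That is stated for group 1 and inferred here because it returns the printed number.

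n = 1.96² × Se(1 − Se) / (d² × prevalence)

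- 3%: 3.8416 × 0.1476 / (0.01 × 0.03) = 1890
- 4%: 1417; 5%: 1134; 10%: 567
- Specificity at 3%: 3.8416 × 0.81 × 0.19 / (0.01 × 0.97) = 61, so sensitivity governs.
- Group 1 by the same formula: 3.8416 × 0.93 × 0.07 / (0.05² × 0.20) = 500, as printed.

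So 1890 is the 3% case. It implies 1890 × 0.03 = 56.7 known cases, and 1.96 × √(0.1476 / 56.7) = 0.100. There is no slack.

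**2. The same N with status unknown.** I used a two-class model with four tests (POC strip plus three references), conditionally independent given true status. Its 9 parameters (prevalence, four sensitivities, four specificities) are all unknown, with no prior information. The half-width is 1.96 times the standard error of POC sensitivity from the inverse expected Fisher information at N = 1890. The N needed for 10 points is 1890 × (half-width / 10)². Reference accuracies are **assumptions**, in the order copro-antigen, PCR, rES33 blot. Half-widths are in percentage points.

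| Assumed reference Se/Sp | 3%, all verified | N for 10 points at 3% | 3%, half of POC negatives verified | 5%, all verified | 10%, all verified |
|---|---|---|---|---|---|
| 0.99/0.999 each | 10.0 | about 1,890 | 13.5 | 7.7 | 5.5 |
| 0.95/0.99, 0.90/0.999, 0.95/0.99 | 10.1 | about 1,940 | 13.7 | 7.8 | 5.5 |
| 0.90/0.97, 0.80/0.995, 0.90/0.97 | 10.8 | about 2,210 | 14.6 | 8.2 | 5.7 |
| 0.85/0.95, 0.70/0.99, 0.85/0.95 | 12.1 | about 2,750 | 16.3 | 9.0 | 6.1 |
| as above, but rES33 blot like the strip (0.82/0.81) | 13.1 | about 3,240 | 17.7 | 9.8 | 6.7 |
| 0.80/0.92, 0.60/0.99, 0.80/0.90 | 14.2 | about 3,820 | 19.3 | 10.5 | 7.0 |

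Another weak set (Se 60–82%, Sp 90–98%) gives 15.0 points at 3% with all verified.

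**3. Why subsampling matters.** At 3% prevalence about 0.18 × 56.7 = 10 infected patients are expected among about 10 + 0.81 × 1833 = 1495 POC negatives. Verifying half of the negatives sees about half of those 10. The one-half is assumed. With a quarter verified, the 3% half-width runs from 18.6 to 26.6 points over the same scenarios.

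**4. Shared antigen.** The T strip and one reference both use rES33 (sections 2.1 and 2.3), so conditional independence is doubtful. Allowing dependence between them at half its maximum gives 10.0 to 15.8 points at 3% with all verified, over the scenarios other than the fifth row.

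**The case against.** **There is no arithmetic error.** This stands. The inputs return 1890 to the unit, and the article calls the 10% a desired precision. The point is that the formula does not match the analysis, not that a sum is wrong.

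**3% is one corner of the range.** This stands and limits the claim. A reader might infer that the T interval will be wider than stated whatever the prevalence. The documents do not support that. The one local figure is 5.2% by copro-antigen ELISA in Songwe (Introduction), though not in these patient groups. At 5.2% with full verification the half-width is 7.6 to 10.2 points over the tabulated scenarios. The 3% condition remains relevant because the size was set there.

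**The loss depends on assumed accuracies.** This also stands. With near-perfect references the loss from unknown status is negligible, and all 2000 patients would then give 9.7 to 9.9 points, though only by spending the contingency. In the four weaker rows, 2000 evaluable patients still give 10.5 to 13.8. The Introduction itself says that copro-antigen ELISA, recombinant immunoblot and PCR have performance limitations.

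**Model and priors may be in the cited sources.** This stands in part. Informative priors could recover precision, and their absence from an article is not a fault. But the printed 10% comes from a formula with 57 known cases and no prior, so it does not describe such an analysis either.

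**Partial verification is the larger loss.** This is true when half or fewer of the negatives are verified. It adds to the loss from unknown status and does not replace it.

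**Conclusion.** The concern holds in a limited form. At 3% prevalence, and without informative priors, the stated 10 points is the best the planned analysis can do. With every patient verified and conditional independence, the half-width is about 10 to 15 points, depending on assumed reference accuracies. With half of the POC negatives verified, also an assumption, it is about 14 to 19 points.

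With full verification the 10-point target is met at about 5% prevalence in all but the weakest tabulated scenario, and at 10% in all of them.

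Two further inferences are tempting and not supported. One is that the trial needed some specific larger number of patients: the required N at 3% runs from about 1,890 to beyond 3,800 on inputs that the documents do not give. The other is that 11 to 15 points is the correct figure to print: that range leaves out the favourable reference scenarios and assumes full verification, which the design excludes.

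The stated precision should be corrected. Recruitment ended in February 2020 (section 2.2), and nothing here calls for a change in the sample size or the analysis.

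**What to change.** Keep the sample size. In section 2.11, replace the stated 10% precision for T with the expected half-width for T sensitivity, obtained by simulating the planned no-gold-standard model. The simulation should:

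- span 3% to 10% prevalence;
- use stated sensitivities and specificities for the three references, with their source;
- apply the actual stage 2 sampling fraction of POC negatives and the planned weighting;
- use the priors of the planned model, if it has any, and include a case with dependence between the T strip and the rES33 immunoblot.

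Report the result by prevalence, and say that 1890 is the known-status figure at 3%. Do not print a range from this review as the corrected value, because it rests on assumed inputs.

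The cost is a short simulation and a less favourable stated figure at low prevalence. It needs no extra patients.
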